### Statistical Analysis

The primary endpoint for the biometrical evaluation (responsible statistician: CM) is the PANSS-Positive-Score of the Positive and Negative Syndrome Scale at the time of 9 months after inclusion. It will be analysed after completion of T9-assessments.

The statistical hypothesis for the confirmatory test of the primary endpoint is that the treatment groups are significantly different when analysed using multilevel linear mixed models with treatment and study centres as levels of analysis and adjustment for baseline values. The decision for maintaining or rejecting the null hypothesis will be made applying a two-sided test with α = 0.05. A two-sided test will be chosen as the published results about the comparison of CBT and ST are inconsistent. The observed effects will be described by use of means including the appropriate (one-sided) 95%-confidence intervals.

The confirmatory statistical evaluation of the efficacy of the CBT in this trial will be restricted to the primary endpoint. Only the rejection of the null hypothesis will be interpreted as statistical evidence for the efficacy of CBT. The confirmatory statistical analysis will be based on the intention-to-treat principle (ITT). In addition, a "per protocol" (PP) analysis will be conducted

All secondary endpoints will be compared and statistically assessed for descriptive purposes and not in a confirmatory sense. The aim of the analysis is explorative data analysis, not hypothesis testing or generation of evidence for efficacy. Because of the explorative character of this part of the analysis, no a priori statistical analysis plan exists. If adequate, secondary endpoints will be compared and statistically assessed using covariance techniques with baseline values and centers as covariates. Changes of scores over time will be modeled using linear or non-linear or nonparametric models as adequate. In addition, appropriate statistical methods of explorative data analysis including graphical methods and descriptive statistics will be used. No interim analysis and no subgroup analyses are planned.

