### Sample size calculation

The primary endpoint analysis will be conducted with linear mixed models (LMM, [35]). As software for sample size calculation for the analysis of longitudinal data using multilevel mixed models is not available, we calculated the sample size for classical ANOVA using nQuery 4.0.

The power calculation is based on published results about CBT for persistent positive symptoms. For the comparison between CBT and TAU Tarrier et al. [36] reported Effect Sizes (ES: (mean_TAU_-mean_CBT_)/SD_TAU_) of 0.33-0.66 for the 18 month follow-up. Tarrier et al. (1998) found an ES of 0.48, Kuipers et al. [37] an ES of 0.6, and Sensky et al. [19] an ES of 0.5. In a review Gould et al. [38] found a range of ES from 0.2 to 1.26. The reported variance differs to a great extent indicating considerable differences with regard to samples or treatments. A recent effect size analysis applied broader inclusion criteria for studies and resulted in an ES of .57 for acute patients (post-treatment analysis) and an ES of 0.27 in chronic patients [3]. These reviews show considerable efficacy of CBT when compared to treatment as usual. However, this study focuses on the difference between CBT and Supportive Treatment (ST). Unfortunately, the power calculation is more difficult for this comparison as fewer studies are available. According to a review of Tarrier et al. [36] the following studies have included ST-control groups: Tarrier et al. [18], Haddock et al. [28], Pinto et al. [39], Lewis et al. [40], and Durham et al. [41]. The effect sizes vary between -.49 in a study including only 21 patients [28] and .99 in a study with 37 patients [39]. In addition, sample characteristics and endpoints are different between the studies. Thus, it does not seem possible to make assumptions about the ES for the comparison between CBT and ST based on the literature.

Regarding drop out rates there is also much heterogeneity with a range between 0% and 36% [36,38]. The majority of studies reports drop out rates of less than 20%. As measures of quality control will be applied and monetary incentives for participation in the follow-up examinations will be offered we expect a drop out rate of about 20%.

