On this background we aim to identify an effect size of more than .35 as significant given an anticipated drop out rate of 20%. An ES of .35 would be obtained if the PANSS Scores (Positive Syndrome) at the post treatment assessment were 12 for CBT and 14.5 for ST with a standard deviation of 7.14. An ES of less than .35 would be of limited clinical relevance.

This results in n = 130 per group for a power of 80% and a two-sided significance level of 5% (sample size calculated by nQuery 4.0, Panel MGT0). The confirmatory statistical analysis will be based on the intention-to-treat principle. Patients with missing PANSS-scores at T9 (post-treatment) will be included with the last observation carried forward (LOCF). In case of missing PANSS-scores at T9 the treatment effect will presumably be underestimated by using LOCF. To compensate for this underestimation the sample size should be adapted for drop out. Thus, we plan to include 330 patients (165 per study condition).

As assumptions about the real effect size cannot be based upon the literature we calculated different scenarios: in case of a lower effect size and/or drop out of more than 20% the statistical power will be reduced. For example, a reduced ES of 0.2 would result in a power of only 36% for the drop out of 20%. An increased drop out of 30%would reduce the power to 74% for the minimum ES of .35. On the other hand, a more favourable ES of 0.45 would increase the power to 85% for the maximum drop-out rate of 20%.

With a sample size of 330 individuals (165 each therapy group), ten assessments per patient, one primary analysis variable (therapy) and one covariable (center), the power should also be sufficient for a Mixed Model [42].

Table 3 gives an overview over the number of patients required in the different stages of the trial and the required effort for treatment and assessment. In order to successfully include 330 patients 6 study centers have been included which were committed to participate actively in this trial.

**Table 3 T3:** number of patients required in the different stages of the trial

	total	per center
required number of eligible patients (with 75% refusal)	1304	217
number of patients to be included (incl. 20% drop out)	330	55
number of patients to be analysed (ITT, LOCF)	330	55
number of patients to be analysed per protocol	260	44
treatment sessions (CBT and ST)	5530	922
number of visits	4620	770

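### The confirmatory test is two-sided at 5% but the planned confidence interval is one-sided at 95% with no side named, so interval and test can disagree and one limit is missing

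*Protocol article*

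**What the plan says.** All the main statements are in the Statistical Analysis section of the protocol article.

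- Test: "The decision for maintaining or rejecting the null hypothesis will be made applying a two-sided test with α = 0.05".
- Reason for two sides: "A two-sided test will be chosen as the published results about the comparison of CBT and ST are inconsistent".
- Interval, in the very next sentence: "The observed effects will be described by use of means including the appropriate (one-sided) 95%-confidence intervals".
- Evidence rule, in the following paragraph: "Only the rejection of the null hypothesis will be interpreted as statistical evidence for the efficacy of CBT".

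The Sample size calculation section is two-sided as well: "This results in n = 130 per group for a power of 80% and a two-sided significance level of 5" per cent. It treats effect sizes below 0.35 as of limited clinical relevance, and it reports earlier CBT-versus-ST effects ranging from -0.49 to 0.99. The Lines of interpretation section reads a non-significant primary result as showing that CBT has no specific effect on positive symptoms.

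Nowhere does the article say which side of the interval is bounded. Nor does it use a one-sided level of 97.5%, which would bring one limit into line with the test.

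**The concern.** A confidence interval is normally read as the companion of its test: zero lies outside it exactly when the test rejects. That link is broken here. A one-sided 95% interval belongs to a one-sided 5% test, and the plan rejects a one-sided test for a stated reason, the inconsistent direction of earlier results.

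Two things are at stake. First, a report could show an interval that excludes zero beside a primary test that did not reject. Second, only one limit is reported. To support superiority, a reader needs the limit nearer to zero. To support the strong reading of a null result in Lines of interpretation, a reader needs the limit on how large the benefit could still be, set against 0.35. A one-sided interval gives one of these, and the article does not say which.

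**Working it through.** **Inputs.** Two-sided α = 0.05 and one-sided 95% interval (Statistical Analysis). Planning values for the PANSS positive score: "were 12 for CBT and 14.5 for ST with a standard deviation of 7.14" (Sample size calculation). Number analysed by intention to treat with LOCF: 330, so 165 per arm (Table 3). As a sensitivity case, 132 per arm, which is 165 × 0.8 with the planned 20% dropout removed.

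**1. Reproduce the plan's own figure.** ES = 2.5 / 7.14 = 0.350. By the normal formula, n per arm = 2(1.960 + 0.842)² / 0.35² = 128.1, so 129. The t-test version gives 129.0 to 129.1, rounded up to the stated 130. A one-sided 5% calculation would give 2(1.645 + 0.842)² / 0.35² = 100.9, so 101. The trial was therefore sized two-sided.

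**2. Compare the thresholds.** Let the difference be CBT minus ST, so that negative values favour CBT, and let z be the estimate divided by its standard error, counted positive in favour of CBT. The one-sided 95% upper limit is below zero when z > 1.645. The two-sided test rejects in favour of CBT when z > 1.960. They conflict for 1.645 < z < 1.960, which is two-sided p between 0.05 and 0.10.

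**3. An example on the planning scale.** SE = 7.14 × √(2/165) = 0.786. Take z = 1.80:

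- difference = -1.80 × 0.786 = -1.41 points, about 0.20 SD; two-sided p = 0.072, so the null hypothesis is maintained;
- one-sided 95% upper limit = -1.415 + 1.645 × 0.786 = -0.12, which excludes zero;
- two-sided 95% interval = -1.415 ± 1.541 = -2.96 to 0.13, which includes zero.

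**4. Chance of a conflict if the upper limit is the one reported.** P = Φ(1.960 - δ) - Φ(1.645 - δ), with δ = ES × √(n/2).

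| True ES | 165 per arm | 132 per arm |
|---|---|---|
| 0 | 2.5% | 2.5% |
| 0.2 | 12.5% (δ = 1.82) | 12.3% (δ = 1.62) |
| 0.35 | 4.9% (δ = 3.18) | 7.3% (δ = 2.84) |

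**5. What each choice of side can show (165 per arm).** The one-sided margin is 1.645 × 0.786 = 1.29 points, or 0.181 SD. The two-sided margin is 1.960 × 0.786 = 1.54 points, or 0.216 SD.

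| Interval for CBT minus ST | Can exclude zero in favour of CBT | Can exclude a benefit of 0.35 SD |
|---|---|---|
| Upper limit only | Yes, already at z > 1.645 | No, benefit has no limit |
| Lower limit only | No | Yes, if observed ES is below 0.35 - 0.181 = 0.169 |
| Two-sided 95% | Yes, exactly when the test rejects in that direction | Yes, if observed ES is below 0.35 - 0.216 = 0.134 |

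**The case against.** The best reply is that the interval only describes. The plan ties the efficacy claim to the test: "Only the rejection of the null hypothesis will be interpreted as statistical evidence for the efficacy of CBT". An interval that excludes zero beside a failed test therefore cannot count as evidence under the plan's own rule. The sample size, primary model, estimate and type I error are all untouched, and anyone with the estimate and its standard error can compute the two-sided interval. All of this stands, and it settles the severity. It does not remove the contradiction, because the article states the one-sided interval outright and this is not a detail left to a fuller document.

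Four stronger readings are tempting and are not supported:

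- **That the false-positive rate of the trial is inflated.** The decision rests on the two-sided test alone, so it is not.
- **That the interval can never inform a null result or exclude 0.35.** This holds only if the limit faces zero. With the benefit side bounded, it can do both. The article does not say which is meant.
- **That rejection in favour of ST would count as evidence for CBT.** The evidence sentence states a necessary condition, and Lines of interpretation ties evidence for specific efficacy to CBT being superior.
- **That the interval is wrongly attached to arm means.** The sentence speaks of observed effects, which suggests the difference. If arm means were intended, exclusion of zero would have no meaning and the conflict described here could not arise. The two complaints cannot both stand, and the point does not rest on this one.

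**Conclusion.** The plan is inconsistent as written: a two-sided 5% test, justified by uncertainty about direction, is followed at once by a one-sided 95% interval with no side named. The consequence depends on the side. With the limit facing zero, interval and test disagree for z between 1.645 and 1.96, and the size of the benefit has no limit. With the benefit side bounded, superiority of CBT cannot be shown from the interval.

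The conflict probabilities (2.5%, about 12.5% and about 4.9% at 165 per arm) are chances that a descriptive interval and the test look discordant. They are not decision errors. They assume the first choice of side and a simple two-mean comparison; the baseline-adjusted mixed model will have a different standard error, which would shift the figures for non-zero effects. The figures in points also assume the planning SD of 7.14 on the summed scale, whereas the Primary Endpoint section defines the score as the mean of the seven items. The thresholds 1.645 and 1.96 depend on none of this. Severity is minor to moderate: reporting and interpretation are affected, the confirmatory decision is not.

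**What to change.** In Statistical Analysis, replace the one-sided interval with a two-sided 95% confidence interval for the adjusted CBT-ST difference at T9, taken from the primary model. It then agrees with the test and gives both limits, so that a null result can be judged against 0.35.

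The cost is one sentence and a wider margin: 1.96 instead of 1.645 standard errors, or 1.54 instead of 1.29 points on the planning scale at 165 per arm. Sample size, test and trial conduct do not change.

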### Medication

Regarding psychopharmacological treatment the study is open and requires no restriction of treatment. The sample size of this trials justifies the expectation of equal distribution of type (classical vs. atypical antipsychotics), dose, rate of non-adherence to medication, prescription of other psychopharmacological treatment (antidepressants, mood stabilizers, benzodiazepines) in both treatment groups.

However, both the medication dose and the medication compliance are potential confounders which have to be controlled for. In particular, it could be the case that medication will not be completely independent from the study condition. As medication has the potential to influence the course of symptoms it is important to observe the medication carefully to allow for detailed analysis of this aspect. Medications and doses will be documented monthly. Side effects will be assessed at baseline as well as at the post-treatment assessment T9.

Medication compliance [43] will be rated monthly along a 7-point scale (with 1 = total rejection of medication, and 7 = active cooperation and full acceptance of medication).

### Assessment of adherence to treatment manuals

To evaluate the adherence to the manuals a number of measures will be assessed. First, in order to systematically assess characteristics of form and content as well as aspects of adherence of treatment therapists filled in structured session reports after each treatment session. The session reports give information whether the treatment session was conducted as scheduled or cancelled by the patient and whether the session began on time or delayed. Further, the session reports show the duration of the session, the primary and secondary foci of intervention (e.g. establishing treatment goals, work on delusions), the use of manualized treatment material, reasons for non-adherence to the agenda (e.g. due to symptomatic worsening, focus on current problems, non-compliance of patient or other reasons), accomplishment of homework by the patient, and the cooperation of the patient as rated by the therapist. The cooperation rating scale is a fully anchored ordinal scale with 1 = excellent, 2 = adequate, 3 = sufficient, and 4 = poor. The session reports will be available for all sessions conducted. An individual study therapy will be considered as having been conducted according to manual if a patient has attended at least 14 treatment sessions. Further, two thirds of the sessions conducted have to fulfil the following criteria: duration >40 and <60 minutes, use of manualized treatment materials or strategies, and at least sufficient cooperation of the patient.

Second, all treatment sessions (CBT and ST condition) will be audio taped if patients give their consent. A maximum of four audio tapes of each patient will randomly be selected for analyses: one of the first 3 sessions (early phase), one of the sessions 4-10 (early middle phase), one of the sessions 11-17 (late middle phase), and one of the last 3 sessions (late phase). This procedure is independent of the actual number of treatment session a patient has participated in. The audio tapes will be checked with regard to manual adherence. Guided by a checklist it will be assessed whether or not the treatment session followed the CBT or the ST manual with regard to content, the material worked on, and the formal characteristics (e.g. duration of the session). The ST checklist also comprises items regarding an irregular application of CBT-specific techniques. Our adherence checklists will be subjected to analysis of interrater reliability. Since mistrust and paranoia are core symptoms of chronic psychotic disorders, we expect a rate considerably below 100% of patients who give their written informed consent for audio taping their therapy.

### Assessment of unspecific mechanisms of action

According to Orlinsky's and colleagues' review [16] the strongest evidence linking process to outcome concerns the therapeutic alliance. Therapeutic alliance proved to be a common ingredient of all psychotherapeutic interventions [44] and to be at least modestly correlated with outcome [45,46]. The therapeutic alliance as well as other unspecific mechanisms of action (e.g. clarification, activation of resources, emotional involvement, problem solving) will be assessed using the Bernese Post Session Reports [47] for patients (BPSR-P) and therapists (BPSR-T). In the framework of the German Research Network on Schizophrenia we conducted factor analyses of both instruments in a sample of 111 first episode patients with schizophrenia participating in CBT for relapse prevention. We identified dimensions relating to the therapeutic alliance, therapy progress, emotional involvement, dissatisfaction with therapy, and others. Both instruments will be applied at the end of each therapy session of the CBT and the ST condition. The continuous application of the session reports will allow examining the course of the above mentioned unspecific therapeutic mechanisms during the CBT and ST. We expect no differential course of these unspecific factors between the two treatment conditions.

### Assessment of therapist's competence

Establishing empirical collaboration between the patient and the therapist as a means for cognitive restructuring is a major aspect of the therapists' competence in CBT. To measure the extent of empirical collaboration the four randomly selected audio tapes will be analysed by means of the Cognitive Therapy Scale for Psychosis [CTS-Psy; [48]]. The CTS-Psy consists of two subscales each with five items. The items are rated on the original nominal scale (1 = appropriately included, 0 = inappropriately omitted, and 9 = appropriately omitted) as wells as on a 5-point interval scale where higher scores indicate better competency. We designed this 5-point Likert-scale to prevent potential ceiling effects. Scale I "general skills" includes the items agenda setting, feedback, understanding, interpersonal effectiveness, and collaboration; scale II "specific skills" covers guided discovery, focus on key cognitions, choice of intervention, homework, and quality of intervention. The specific skills will be measured only in the CBT condition. The CTS-Psy demonstrates excellent inter-rater reliability, good validity, and sensitivity to changes [48]. Furthermore, we will conduct own analyses on the interrater reliablity of our German adaptation of the CTS-Psy.

Regarding the application of general skills we expect no difference between the CBT and the ST condition. Further, according to the rationale of CBT, we hypothesize that the quality of a therapist's specific skills correlates with therapeutic outcome (symptom reduction) in the CBT condition.

The research addressing treatment adherence, the unspecific mechanisms of action, as well as the therapist's competence are integrated within the sub-project "Process and outcome in CBT for positive symptoms in psychotic disorders" (PI: AW).

### Assessment of safety of interventions during the treatment phase

Safety of psychological intervention in schizophrenia has been assessed in terms of suicide rates and rates of serious symptom deteriorations. The Cochrane Reviews on Family Intervention [49], on Cognitive Behavioural Treatment of Positive Symptoms [50], on Cognitive Remediation [51], and on Psychoeducation [52] could demonstrate that neither the suicide rate nor the rate of relapse was increased in psychological intervention. The same result was reported by Tarrier et al [7] who conducted the most subtle analysis yet on this topic and included also an ST condition in their study. Thus, there is no indication in the literature for an increased risk for patients as a consequence of their participation in the treatment described in this protocol. However, based on clinical experience it seems important to consider the following major risks:

(a) Increase of positive symptoms as a consequence of therapeutic overstimulation: It is known that positive symptoms may increase if the psychosocial stress is greater than the coping ability of a patient. Thus, a forced therapeutic approach may represent stress for a patient increasing the risk for symptom exacerbation.

(b) Suicide, suicide attempt or suicidal crisis could occur as a consequence of dysfunctional coping with the negative psychological and social consequences of the disorder.

However, this study provides optimal conditions to prevent major risks, to detect symptom exacerbations early, and to intervene early and sufficiently. (a) The symptoms are assessed frequently in short intervals by the rater as well as by the study therapist. (b) Therapists are trained to react to symptom deterioration. They will adapt their strategy to the patients' needs. This is completely compatible with the treatment manual. (c) The therapist will discuss the treatment strategy with clinically experienced supervisors. (d) A psychiatrist responsible for routine care is involved in the treatment. Independent of the study this psychiatrist will initiate crisis intervention whenever required.

As described above there is no indication for specific risks or enhanced rates of adverse events as a consequence of participation in CBT or ST. However, as the safety of interventions for positive symptoms in schizophrenia have not been studied extensively this study will control for severe symptom exacerbations and suicidal crises as adverse events.

Severe adverse events to be observed at every assessment throughout the trial are:

• Death caused by suicide

• Suicide attempt

• Suicidal crisis (explicit plan for serious suicidal activity without suicide attempt) as defined in Calgary Depression Rating Scale for Schizophrenia [CDSS; [27]], item 8, rating 2)

• Severe symptomatic exacerbation, defined by the Clinical Global Impression Scale (CGI) which includes ratings of illness severity, changes in overall clinical status, and therapeutic effects. A rating of CGI2 ≥ 6 and CGI 1≥ 6 would be regarded as severe adverse event.

The safety parameters are part of the regular clinical follow-up examination conducted by the study rater every four weeks. In addition, study participants remain in their usual routine outpatient treatment and will therefore see their independent psychiatrist regularly. The routine care psychiatrist and the study therapist are requested to exchange information about the status of the patient and to provide an optimal individual treatment. The study rater will communicate any information about adverse events to the routine care psychiatrist and the study therapist. Thus, the study provides an optimal framework to immediately detect any complication in the treatment.

Information about the safety parameters is recorded in the CRF every four weeks by the study rater. In addition, therapists are requested to assess the safety parameters in every session and to record their assessment in the session protocol.

The observation of these events should result in a statistical remarkable result, if the incidence of events in one of the two groups will be higher than in the other group. The statistical observation will be done for a significance level of α = 0.2 (two sided) and a power of 0.8 with the help of the software PEST (distributed by Whitehead).

Analyses will be conducted three times: after 100, 200 and 300 patients reaching T3. When analysing the safety data, the full observation period of all patients and all available data will be considered. The safety analyses will be conducted by a statistician (CE) not involved in the design and analysis of this trial, using coded group labels A and B blinded for the real therapy groups.

The results will be reported directly to the members of the independent advisory board. In case of rejection of the null hypothesis of equal incidence rates in the two groups, the advisory board will decide whether or not the study has to be stopped.

We do not expect any difference regarding illness related events between the groups.

